## Objective three

Patient’s degree of satisfaction of euthyroidectomy done under the two arms will be measured by satisfaction scale of 1/2/3/4/5 where 1 = very dissatisfied, 2 = dissatisfied, 3 = neutral, 4 = satisfied, and 5 = very satisfied.

The satisfaction will also be assessed basing on willingness to undergo a new operation (euthyroidectomy) under the same type of anesthesia. Since the satisfaction score is a Likert ordinal scale, the proportions for satisfaction scores will be computed for both arms (LA and GA) and the difference in proportions will be compared using the non-parametric test of Kruskal–Wallis (H).

### Loss to follow-up

To minimize loss to follow-up, participants will be given contacts of the study nurse coordinator who will also play a role in making reminder phone calls of those who are due for review (appointment). For those unable to come to hospital, one planned home visit will be conducted. A participant will be regarded as lost to follow-up if he or she is untraceable by hospital clinic, phone call, and home visit.

### Missing data

Values will be imputed for participants with missing end points such as withdrawals, lost to follow-up, and crossovers. The baseline clinical and sociodemographic characteristics of participants in this category will be compared between the two groups.

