### Interventions: modifications

#### Adverse events and trial discontinuation for individual participants

The participants are anticipated to experience pain discomfort and or other complications due to the surgery as the main treatment for goiter not because of the study. In addition to breach of trial protocols, too much pain during surgery using LA will result in converting to GA (cross over) and advancing to stronger analgesics other than prescribed in protocol with ultimate discontinuation of individual participant from the trial.

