### Sample size estimation

Sample size estimation in this study assumes a null hypothesis that there is no difference in early post-operative outcomes for euthyroidectomy under LA versus GA (equivalence study). In a study that evaluated the measurement of acute post-operative outcomes amongst patients who undergo surgery, a patient acceptable symptom state, i.e., the value beyond which patients considered themselves well, was documented at 33% [28]. Based on a study at the Scott and White Memorial Hospital, in Texas, the proportion of patients who underwent euthyroidectomy under LA with no identifiable complication were 83% as opposed to 79% who underwent GA [16]. Therefore, assuming a statistical power of 80%, type 1 error of 0.05, and a threshold for equivalence in effect with a dichotomous outcome that LA is no better or worse than GA by a minimal clinically important difference of 33% in the primary outcome measures; the sample size estimation based on Cleveland Clinic sample size estimation in clinical research (https://riskcalc.org/samplesize/) [29] will be 26 for each arm (1:1 allocation), including additional 10% to cater for loss to follow-up.

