### Data management and analysis

Data will be coded, entered in Excel version 2016, and later exported to STATA 14.2. for analysis. The intention-to-treat model will be used to minimize bias as way of reflecting what happens in real clinical practice. The intention-to-treat population will be used for inference and will be defined as all eligible randomized patients recruited in this study. Analysis will be done per study objective. Socio-demographic and surgical factors will be summarized descriptively using summary measures as proportions, means, medians, and measures of variation such as standard deviations for means, interquartile range for medians. All analyses will be computed at 95% confidence intervals and regarding *p* < 0.5 as statistically significant.

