### Individual discontinuation

Other than breach of trial protocols due to non-adherence, too much pain during surgery using LA will result in converting to GA (cross over) and advancing to stronger analgesics in the post-operative period other than prescribed in protocol. This will result in ultimate discontinuation of individual participant from the trial.

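### LA participants converted to GA are discontinued and their end points imputed, although their outcomes could be observed and the plan promises intention-to-treat

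*Protocol article*

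**What the plan says.** On the analysis population, the Data management and analysis section states: "The intention-to-treat population will be used for inference and will be defined as all eligible randomized patients recruited in this study". It gives the reason as well: "The intention-to-treat model will be used to minimize bias as way of reflecting what happens in real clinical practice".

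Two other sections deal with LA that fails during the operation. Adverse events and trial discontinuation for individual participants says that "too much pain during surgery using LA will result in converting to GA (cross over") and to stronger analgesics than the protocol prescribes, "with ultimate discontinuation of individual participant from the trial". Individual discontinuation repeats the rule for the same event: "This will result in ultimate discontinuation of individual participant from the trial". Both sections also name breach of the protocol as a ground. Neither describes a conversion from GA to LA.

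The Missing data section then says: "Values will be imputed for participants with missing end points such as withdrawals, lost to follow-up, and crossovers". It names no imputation method.

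**The concern.** A converted patient has not disappeared. The operation takes place in the camp and the patient recovers under care there. The end points become missing only because the protocol takes the patient out of the trial. The analysis then fills in values for people whose outcomes could have been recorded.

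Conversion is also part of the answer to the trial's question. The Study rationale asks whether LA is a workable alternative where anaesthesia staff and facilities are scarce, and an operation that starts under LA and ends under GA bears directly on that. Such a patient uses the resources of both techniques and has a particular view on satisfaction and on accepting the same anaesthetic again. If these outcomes are replaced by values typical of LA operations that went to plan, the LA arm will look better than it was.

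**Working it through.** **1. The rules side by side**

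| Section | Treatment of a converted LA patient |
|---|---|
| Data management and analysis | Counted, as an eligible randomized patient, to reflect real practice |
| Adverse events and trial discontinuation; Individual discontinuation | Discontinued from the trial |
| Missing data | Classed with withdrawals and losses; value imputed |
| Primary outcome measures; Table 1 | Assessments at 6, 12 and 24 h and 30 days, with no exception for conversion |
| Loss to follow-up | Not lost: that term is kept for people who cannot be traced by clinic, phone or home visit |

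The first three rows can all be followed at once only if the denominator is kept and the observable outcome is given up. Objective one adds a further ambiguity: its denominator is the number of operations done under each technique, which can be read as grouping patients by technique received.

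**2. The plan's own figure**

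Inputs from Sample size estimation: "the proportion of patients who underwent euthyroidectomy under LA with no identifiable complication were 83% as opposed to 79% who underwent GA"; "assuming a statistical power of 80%, type 1 error of 0.05"; margin 33 points; 10% added for loss to follow-up; 26 per arm.

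With one-sided 0.05 and the type 2 error not split between the two bounds:

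n = [0.83 × 0.17 + 0.79 × 0.21] × (1.645 + 0.842)² / (0.33 − 0.04)² = 22.6, so 23 per arm; 23 / 0.9 = 25.6, so 26.

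The stated 26 is reproduced under that reading. The 10% is for loss to follow-up; Study strengths and limitations adds withdrawal. Neither section mentions conversions.

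**3. Possible size of the distortion**

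Assumptions, none of them from the documents except the 83% and 79%:
- c = share of LA patients converted, 5% to 20% (about 1 to 5 of 26).
- Non-converted LA patients are 83% complication-free, and imputed values have the same rate.
- q = true complication-free rate in converted patients.

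True LA rate = 0.83(1 − c) + qc. Rate after imputation = 0.83. Overstatement = c(0.83 − q).

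| c | q = 0 (all have a complication) | q = 0.50 (half do) | q = 0.79 (as GA) |
|---|---|---|---|
| 5% | 4.2 points | 1.7 | 0.2 |
| 10% | 8.3 | 3.3 | 0.4 |
| 15% | 12.5 | 5.0 | 0.6 |
| 20% | 16.6 | 6.6 | 0.8 |

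After imputation the LA minus GA difference stays at 0.83 − 0.79 = +4 points in every cell. The true difference is 4 points minus the overstatement. It changes sign above c = 0.04 / 0.83 = 4.8% when q = 0, and above c = 0.04 / 0.33 = 12.1% when q = 0.50. It does not change sign in this range when q = 0.79. In patients, with q = 0, one conversion of 26 leaves 0.83 × 25/26 − 0.79 = +0.8 points, and two leave 0.83 × 24/26 − 0.79 = −2.4 points.

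Against the margin, the largest cell is 16.6 / 33 = 50% of it, and the q = 0.79 column is at most 0.8 / 33 = 2.4%.

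**The case against.** The defence has several good points.

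- **The denominator is kept.** Imputing crossovers leaves every randomized patient in the analysis. A reader might infer that converted patients are dropped from the intention-to-treat set; the Missing data section does not say that. What is lost is their observed outcome.
- **The imputation rule is conditional.** It covers participants whose end points are missing and does not say that recorded values will be overwritten. This would settle the matter if converted patients stayed under observation, but two sections discontinue them from the trial itself, not merely from the allocated technique.
- **Intraoperative pain is not the primary outcome.** A reader might infer that the rule selects on a primary outcome and removes the worst LA results. The trigger is pain during surgery; the primary outcomes are post-operative. After GA and stronger analgesics, later pain scores could be higher or lower, and the article links intraoperative pain to neither hematoma, voice change nor infection.
- **Only pain conversion is confined to LA.** Breach of protocol can occur in either arm. Stronger analgesics are described as following conversion, not clearly as a separate ground.
- **No method is named.** That detail may be left to an analysis plan. A worst-case rule, or a model that uses conversion status, need not favour LA. It therefore cannot be stated as fact that values will be borrowed from successful LA patients.
- **Some data will exist anyway.** Part C of the questionnaire records intraoperative events, and costs come from case files.

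These points limit what can be said about size and direction. They do not explain why an obtainable outcome should be classed as missing.

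**Conclusion.** The concern holds in this form: discontinuing converted LA patients and imputing their end points gives up outcomes that the existing schedule could supply, and so defeats the purpose for which the article adopts intention-to-treat. This rests on stated rules, not on an omission.

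A tilt towards LA is likely if imputed values resemble those of non-converted LA patients, most plausibly for satisfaction, willingness to repeat, cost and pain. Its size cannot be established. The ranges of 4 to 17, 2 to 7 and under 1 point depend on an assumed conversion rate, an assumed outcome after conversion and an assumed imputation value. The upper range is a worst case, not an estimate. Even that worst case is about half of the 33-point margin, so the documents do not show that the equivalence conclusion would be reversed. Against the 4-point planning difference, however, a few conversions could change which arm looks better.

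**What to change.** Leave the clinical decision to convert as it is, and reconcile the two discontinuation sections and the Missing data section with the intention-to-treat rule:

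1. State that conversion or a protocol deviation ends the allocated technique but not participation, and that these participants are followed to day 30.
2. Analyse them in the arm to which they were randomized, with observed outcomes and full costs, including those of both techniques. Word the denominator in Objective one to match.
3. Delete crossovers from the imputation rule, so that only outcomes truly not obtained are imputed.
4. Report the number of participants converted.

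A per-protocol analysis may be added as a sensitivity analysis. This fix does not need it, and a per-protocol set would normally leave out the converted patients again.

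The cost is a change of wording: the sample size is unaffected and the assessments are already scheduled. LA results may look slightly less favourable. The article puts recruitment at October 2022 to April 2023, with last follow-up in May 2023. If converted participants have already been discontinued, their outcomes should be sought from the questionnaires and case files, and only what cannot be found treated as missing.

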### Data monitoring committee and auditing for harms

#### Interim analysis

The Kampala International University Western Campus Research and Ethics Committee will form an interim committee that will audit this study and have access to results of interim analysis which will be performed when the 30th patient is recruited (58% of total sample size). The committee will independently recommend continuation, modification, or termination of the study in accordance with its ethical guidelines in relation to safety of human research participants.

Such circumstances warranting termination include unbearable adverse effects or in the unlikely event of achieving differences between study groups. Otherwise, comprehensive results would be published in the final stages of dissemination.

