### Blinding

The outcome data collectors will be blinded on the anesthetic technique, thus single blinding will in effect. The biostatisticians will remain blinded until interim analysis since at this stage, the insights they would offer such when to terminate the study are presumed more important to effective delivery of the trial than the uncertain extent to which they would impart bias in the face of scarce resources [30].

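### The interim look at the 30th patient may stop the trial for a between-group difference with no adjusted threshold, raising the false-difference rate from 5% to about 8% per outcome, and it unblinds the biostatisticians

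*Protocol article*

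**What the plan says.** The Interim analysis section schedules one look, "which will be performed when the 30th patient is recruited (58% of total sample size"). An ethics committee "will form an interim committee that will audit this study and have access to results of interim analysis" and may recommend continuing, modifying or terminating the study, with reference to participant safety. The section then gives the grounds: "Such circumstances warranting termination include unbearable adverse effects or in the unlikely event of achieving differences between study groups". It attaches no boundary or p-value to the second ground.

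The Sample size estimation section sets the error budget once, "assuming a statistical power of 80%, type 1 error of 0.05", and does not mention an interim look. Data management and analysis applies one rule throughout: "All analyses will be computed at 95% confidence intervals and regarding *p* < 0.5 as statistically significant".

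On who knows what, the Blinding section says: "The biostatisticians will remain blinded until interim analysis since at this stage, the insights they would offer such when to terminate the study" are judged to matter more than the uncertain bias they might bring. The same section keeps the assessors masked: "The outcome data collectors will be blinded on the anesthetic technique, thus single blinding will in effect".

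**The concern.** Harm and a between-group difference are listed as separate reasons to stop, so the second works as an efficacy-type stopping ground. The protocol gives the look, its timing, the ground and a single significance level. Followed as written, that means two tests of the same hypothesis at the same nominal level, with nothing taken off the final test.

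Three things are at stake. A false claim of difference becomes more likely than the stated 0.05. A trial stopped at about 15 per arm would report an imprecise and probably exaggerated effect, and would leave the equivalence question unanswered. And biostatisticians who have seen results by arm may still face choices that this document leaves unsettled: pain as a mean score or in strata, a t-test or a rank test, and an unspecified imputation method.

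**Working it through.** **Inputs.** Interim at 30 patients, stated as 58% (Interim analysis). 26 per arm, 52 in total; 83% (LA) and 79% (GA) free of complications; margin 33 points; type 1 error 0.05 (all Sample size estimation). 29 per arm, 58 in total (abstract, Methods). Assumptions: two-sided tests, 15 per arm at the interim, and a stop whenever the interim test is significant.

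**1. The plan's own figure.** 30/52 = 0.577, which rounds to the stated 58%. With the abstract's 58 patients it would be 30/58 = 0.517, so the 58% belongs to a total of 52.

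**2. Type 1 error over two looks.** Under no difference, the interim and final z-statistics are bivariate normal with correlation equal to the square root of the information fraction. With 1.96 at both looks:
- 30/52: correlation √0.577 = 0.760; P(|Z1| > 1.96 or |Z2| > 1.96) = 0.0804.
- 30/58: correlation √0.517 = 0.719; the probability is 0.0825.

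**3. Dependence on the test.** Simulated binary data, 15 then 26 per arm:

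| Test | Event rate | Final look only | Either look |
|---|---|---|---|
| Chi-square | 17–21% | 5.5–5.6% | 8.2–8.6% |
| Fisher exact | 19% | 2.3% | 3.3% |
| Fisher exact | 50% | 2.5% | 3.5% |

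The second look adds error with either test. Only the non-conservative test goes above 5%.

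**4. Precision at the look.** Variance sum: 0.83×0.17 + 0.79×0.21 = 0.1411 + 0.1659 = 0.307. Half-width: 1.96 × √(0.307/15) = 1.96 × 0.143 = 0.280, about 28 points against a margin of 33.

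That uses the planning variance, so it is worth checking with whole patients. At 15 per arm, differences move in steps of 1/15 = 6.7 points, and the largest step inside the margin is 4/15 = 26.7 points. Take 0 against 4 patients with a complication. The pooled proportion is 4/30 = 0.133 and the standard error is √(0.133 × 0.867 × 2/15) = 0.124, so z = 0.267/0.124 = 2.15 and p = 0.032. The Wald 95% interval is 26.7 ± 22.4, that is 4.3 to 49.1 points. This result is a nominal difference with its estimate inside the margin. Its interval crosses the margin, so equivalence is not shown either. With 1 against 5 patients, z = 1.83 and p = 0.068, so the band of such results is narrow.

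**5. Effect of the remedy.** With p<0.001 at the interim (critical value 3.29) and 0.05 at the end, the same calculation at 30/52 gives 0.0501 overall.

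**The case against.** The strongest reply is that this is an equivalence trial, where the false positive that matters most is a false claim of equivalence. Stopping for a difference does not inflate that error; it makes an equivalence conclusion less likely. This stands, and it limits the point to a false claim of difference. That error still counts, because the sample size section words its null hypothesis as no difference and budgets 0.05 against it.

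Second, a boundary may sit in an analysis plan or committee charter that is not shown, and the section can be read as a safety-led, non-binding recommendation. In part this stands: the absence of a boundary alone would be no finding. But the document names difference as a ground beside harm, and its one significance rule covers all analyses.

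Third, the size is modest and depends on the test, as the Fisher results show. This stands.

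A reader might infer more in three places:
- The printed threshold, "regarding *p* < 0.5 as statistically significant", taken literally gives a 50% false-difference rate at the interim and 67% over two looks. The 95% intervals in the same sentence and the 0.05 in the sample size section make a misprint far more likely. It says nothing about the interim design.
- The unblinding might be taken to bias the rest of the trial. The documents do not show that. Outcome collectors stay blinded, the committee recommends independently, the trade-off is disclosed, and the text does not say who runs the final analysis.
- The look might be thought premature because the 30th patient has no 30-day outcome. The section does not say that 30-day data are reviewed, and outcomes at 6, 12 and 24 h would be available early.

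**Conclusion.** The point holds in limited form. The protocol allows a stop for difference at 58% of 52 patients without setting aside any error for it. With an unadjusted 0.05 at both looks and a z-type test, the false-difference rate is about 8.0% per outcome in place of 5% (8.3% for 58 patients). This assumes that a significant interim result leads to stopping. A conservative exact test would keep the rate below 5%, and false equivalence is not inflated. At about 15 per arm a stop could rest on an estimate inside the 33-point margin, leaving equivalence neither shown nor refuted. Unblinding the biostatisticians midway adds a risk of bias in later analysis choices, not a certainty. The text should be changed, but this does not invalidate the design.

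**What to change.** - **Interim analysis.** Limit the look to safety, in line with the committee's stated remit, and delete the difference ground. If it is kept, require p<0.001 at the interim (Haybittle–Peto) and leave the final test at 0.05. Either is a wording change that uses the committee already planned.
- **Blinding.** Have the biostatisticians prepare interim tables by coded arm, with the interim committee holding the key, and keep them blinded until database lock. Coding masks imperfectly, because conversions from LA to GA can occur in one arm only.
- **Time points.** State which assessments the interim reviews. The look can stay at the 30th patient using the 6 to 24 h data. Waiting for 30-day data has a cost: camps are monthly and recruitment spans 4–5 of them. If 52 patients are spread evenly (an assumption), each camp adds about 52/5 = 10 to 52/4 = 13. About 40 to 43 patients could then be enrolled before the look.
- **Separately,** correct the printed significance threshold in Data management and analysis, and reconcile the totals of 52 and 58 so that the 58% has one base.

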### Adverse events

The participants are anticipated to experience pain discomfort such as during local infiltration and or other complications due to the surgery as the main treatment for goiter not because of the study. Any unusual adverse event such as drug reaction presumed to arise from the intervention will be reported to the data monitoring committee, research, and ethics committee of Kampala International University and to the Uganda National Drug Authority.

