### Primary outcome measures

The primary outcome measures will be early 30-day post-operative complications (harms), including: pain, nausea, vomiting, hematoma, transient voice changes, and surgical site infection rates.

The complications will be reported verbally to nursing or to attending physicians for evaluation and recorded on a questionnaire in accordance with MedDRA® version 4.21 standardized reporting on medical and surgical procedures. The post-operative pain will be measured based on visual analogue scale of 0–10 where 0 means no pain and 10 means the worst possible pain. The pain will be assessed at an interval of 6, 12, and 24 h and at 30 days. The mean pain scores will be compared at using Student’s *t*-test, assuming normal distribution; otherwise, medians will be compared using non-parametric Kruskal–Wallis rank sum test.

The nausea and vomiting will be reported to nursing or attending physicians and recorded to the questionnaire using a nausea score on a scale of 0–9 where 0 means no symptom and 9 means very severe. The symptoms will be assessed at an interval of 6, 12, and 24 h and at 30 days. The mean nausea scores will be compared using a paired Student’s *t*-test, assuming normal distribution; otherwise, medians will be compared using non-parametric Kruskal–Wallis rank sum test.

Complications: hematoma, transient voice changes, and surgical site infection rates will be assessed at 6, 12, and 24 h and at 30 days will be reported in accordance with the Clavien Dindo classification of surgical complications [27], where grade I represents complications that do not require any additional intervention, grade II requires pharmacological treatment but not radiological or surgical intervention for instance blood transfusion, grade III requires radiological or surgical re-intervention, e.g., neck exploration and hematoma evacuation, grade IV representing life-threatening complications with at least one organ dysfunction such as respiratory failure that requires intensive care admission. The difference in proportions will be compared using Wilcoxon sum rank test.

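### Reporting to the monitoring committee is tied to unusual events presumed due to the intervention, so serious complications regarded as surgical need not reach it when they occur

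*Protocol article*

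**What the plan says.** Under Adverse events, the rule for sending an event to the committee is: "Any unusual adverse event such as drug reaction presumed to arise from the intervention will be reported to the data monitoring committee". The same sentence sends these events to the ethics committee and the national drug authority. No other section states a duty to send an individual event to the monitoring committee.

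The section on adverse events and trial discontinuation for individual participants tells the reader to anticipate pain and "other complications due to the surgery as the main treatment for goiter not because of the study". Adverse events repeats this statement and gives pain during local infiltration as an example.

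Primary outcome measures makes 30-day complications the primary outcome and grades hematoma, voice change and surgical site infection by severity: "grade III requires radiological or surgical re-intervention, e.g., neck exploration and hematoma evacuation" and "grade IV representing life-threatening complications with at least one organ dysfunction such as respiratory failure that requires intensive care admission". Their stated route is: "The complications will be reported verbally to nursing or to attending physicians for evaluation and recorded on a questionnaire". The committee is not named there.

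Interim analysis says that the committee will audit the study and see the results of one interim analysis, "performed when the 30th patient is recruited (58% of total sample size"). On stopping it says: "Such circumstances warranting termination include unbearable adverse effects".

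**The concern.** The trial asks whether the anesthetic technique changes early complications. A reporting rule that presumes those complications come from the surgery answers that question in advance, and does so for each event before the arms are compared. The example of pain during local infiltration shows the difficulty: under Intervention, that infiltration is the experimental technique.

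The rule also sits badly with the committee's task. The committee may recommend termination for intolerable harm, but the only stated trigger for sending it an event depends on an undefined word (unusual) and on a judgement of cause. It does not depend on seriousness. A severe event that staff regard as a known surgical complication meets neither condition. At stake is how promptly the body that can stop the trial learns of re-operations and life-threatening events, particularly if they gather in one arm.

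**Working it through.** **1. The reporting rule set against the events.** Two conditions must both hold: the event is unusual, and it is presumed to arise from the intervention.

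- Neck exploration for hematoma is the protocol's own example of grade III. Hematoma is a listed primary outcome, so it is anticipated and can be regarded as not unusual. Two sections attribute complications to the surgery, so it can be presumed not to arise from the intervention. Reporting is then not required.
- Respiratory failure needing intensive care is the protocol's example of grade IV. It could be called unusual and linked to anesthesia, and then it would be reported. It could also be put down to surgery, and then reporting is not required. The text does not settle which.
- Seriousness does not appear in the rule, so no grade by itself triggers a report.

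**2. When the committee is otherwise scheduled to see data.** Inputs: look at the 30th recruit (Interim analysis); 52 envelopes (Randomization section); 26 per arm (Sample size estimation); 29 per arm (Abstract).

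- 30/52 = 57.7%, which reproduces the stated 58%.
- Recruits after the look: 52 − 30 = 22. No later look is stated.
- With the Abstract's 2 × 29 = 58 participants the look would fall at 30/58 = 51.7%, with 28 recruits after it. That mismatch in sample size is a separate matter and does not change this point.
- The look is triggered by recruitment, so patients enrolled shortly before it will not yet have had their 30-day assessment.

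**3. How likely a serious event is.** The documents give no grade III–IV rate, so the rate p per patient is an assumption. With equal and independent risk, P(at least one event in n patients) = 1 − (1 − p)^n.

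| Assumed p | Expected in first 30 | P(≥1) in first 30 | P(≥1) in last 22 |
|---|---|---|---|
| 1% | 0.3 | 1 − 0.99^30 = 26% | 1 − 0.99^22 = 20% |
| 2% | 0.6 | 1 − 0.98^30 = 45% | 1 − 0.98^22 = 36% |
| 4% | 1.2 | 1 − 0.96^30 = 71% | 1 − 0.96^22 = 59% |

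The upper end is set by the Introduction, which reports that complications such as hematoma and surgical site infection occur in less than 4% of thyroidectomies under local anesthesia.

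**The case against.** The strongest reply is that the rule does not bar anything. The protocol neither defines unusual nor lists re-operation or respiratory failure as exempt, and in a trial of anesthetic technique a clinician could well report respiratory failure. The committee is also said to audit the study, and a published article may condense a fuller safety section.

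The first part stands as far as it goes: such events *need not* be sent. A reader might infer that they *will not* be sent, or that the committee is blind to harm before the 30th recruit. The text supports neither. But the audit has no stated frequency, listing or duty to supply events, so it does not replace a reporting rule. The point also rests on a restriction that the article states, not on detail left out.

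Four further inferences are tempting and should not be drawn.

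- *Unblinded treating staff apply the test of cause.* The protocol does not say who makes the presumption. Complications go to nursing or attending physicians for evaluation, which makes it plausible, but it is inference.
- *Grade III–IV rates of 10% or 20%.* These fit poorly with the under 4% in the Introduction and with the Sample size section, where 100 − 83 = 17% and 100 − 79 = 21% have any complication at all.
- *A death would have no grade.* The protocol paraphrases a cited scale as far as grade IV. The paraphrase does not show what the full scale contains.
- *The committee needs by-arm listings after every camp.* Complications are the primary outcome, so such listings would be unplanned comparative looks at it, in a trial that may stop if differences between groups are achieved.

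**Conclusion.** The concern holds in a limited form. The stated rule requires a report to the committee only when an event is both unusual and presumed due to the intervention, and two sections tilt that presumption towards surgery in advance. Serious complications that are themselves part of the primary outcome therefore need not reach the committee as they occur. What remains is an audit without a schedule and one look at 58% of 52 recruits, with no look stated for the last 22.

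At assumed grade III–IV rates of 1% to 4%, the chance that at least one such event falls in the first 30 patients is 26% to 71%, and in the last 22 it is 20% to 59%. These figures rest on the assumed rates and on independent, equal risk. They show that the situation is likely enough to need a rule. They do not show that events would be withheld, that harm would cluster in one arm, or that stopping would be justified. The change should be made: it concerns participant safety and costs little.

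**What to change.** - Under Adverse events, drop the two conditions (unusual, and presumed cause) for serious events. Require that every grade III or IV complication, every death up to day 30 and every serious intraoperative event be reported to the committee as it occurs, whatever its presumed cause. The existing wording can stay for non-serious reactions.
- Make the arm available to the committee only, through a route that bypasses the outcome data collectors and the biostatisticians, so that the Blinding section still holds (collectors blinded, biostatisticians blinded until the interim analysis).
- In both places, remove the statement that complications are not because of the study, or reword it to say that they are expected after this operation and that whether their frequency depends on the anesthetic technique is what the trial will assess.

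The cost is a protocol amendment, a short report form and a small amount of extra reporting to a committee already planned. It concerns reporting only and alters no treatment. Routine by-arm comparisons after each camp are not needed.
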